## A description of the measures taken to minimize/avoid bias, including randomization & blinding:

Since the vaccines are administered by different routes (oral for bOPV, and intramuscular for IPV), it is not possible to blind the investigators and the study staff (doctors, nurses, statisticians). However, all serum, oral fluid, and stool samples will be blinded to the laboratory investigators.

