## A diagram of the study design is shown below.

## A specific statement of primary and secondary endpoints:

The primary endpoint is reduction in excretion at days 3,7 and 14 post- challenge dose of vaccine poliovirus administered 28 days after a single dose of bOPV or IPV.

The secondary endpoints are:

- Increase of sIgA in gingival fluids and stools 28 days after a dose of bOPV or IPV.
- Increase in poliovirus antibody secreting cells (measured with ELISPOT) 7 days following a dose of bOPV or IPV.
- Seroconversion or antibody titer boosting 28 days following a single dose of bOPV or IPV.

A description of what kind of trial:

This is a randomized controlled unblinded trial.

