## Maintenance of treatment randomization codes and procedures for breaking codes:

This trial is not blinded.

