## Procedures for accounting for missing, unused, and spurious data:

We will do "Modified Intention to Treat Analysis". All evaluable subjects will be included in the analysis. Evaluable subjects will mean the subjects who complete all study requirements including all study visits and provide sufficient quantities of sera samples for analysis. The subjects where sera are available, but missing a stool or gingival fluid sample, will also be included in the analysis.

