# Data Handling and Record Keeping

The questionnaire data will be double-entered into an electronic data file; the laboratory data will be provided in electronic form and merged based on a common identifier. The original questionnaires will be stored with the Sponsor. Copies of all study documentation, including the questionnaires will be sent to WHO for long-term storage.

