**Description of the roles and responsibilities of the institutions participating**

1. **WHO** will be a funding partner, and has an interest to ensure that the highest possible standards are applied, and that the trial will produce data that will be accepted not only in India, but by regulatory authorities elsewhere. In addition, contribution of WHO will include:
   - 1. Design the study and monitor implementation through visits to the study sites
     2. WHO will provide partial funding (as discussed during the licensing process). Funding would be made available through a technical services agreement to the study site(s) and the laboratory. Funding will include contracting healthcare workers involved in study procedures (physicians, vaccinators, laboratory technicians and others).
     3. SMOs from the National Polio Eradication Program (WHO) will enroll study patients, conduct data collection, supervise adherence to study protocols and standard operating procedures, and monitor processing, storage and transportation of specimens.
     4. Several laboratories from the WHO polio laboratory network in India will process blood and stool samples.
     5. WHO will receive the final clean data set (questionnaire + laboratory data) as soon as available and review report(s) and articles for publication.
2. **The Indian Council for Medical Research** will act as coordinator of the study in India, ensuring quality and safety of study procedures and data collection. The principal investigator, [name] works for the ICMR.
3. **CDC** will provide technical assistance in development of protocol and standard operating procedures, training, statistical analysis, and interpretation of results. CDC will also supervise training, implementation of study procedures and data collection. A CDC laboratory will process isolates from blood, crevicular and stool samples for additional tests measuring antibodies against poliovirus and for quality control of tests conducted in the Indian laboratories.
4. **Panacea Biotec Ltd** assumes roles and responsibilities of the sponsor of the study, including study insurance.
5. **The Ministry of Health and Family Welfare of India** will provide approvals for the study to be conducted and ensure the support of state health authorities.

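### The protocol gives the vaccines' different routes as the reason statisticians cannot be blinded; this does not follow, and it rules out a cheap safeguard against a modest risk.

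*Protocol*

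**What the plan says.** The section on measures to minimise bias gives one reason for leaving staff unblinded: "Since the vaccines are administered by different routes (oral for bOPV, and intramuscular for IPV"). From this it concludes that "it is not possible to blind the investigators and the study staff (doctors, nurses, statisticians"), so statisticians are listed with the clinical staff. It keeps one safeguard: "However, all serum, oral fluid, and stool samples will be blinded to the laboratory investigators".

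The trial is described as open in two other places, "This is a randomized controlled unblinded trial" and, under randomization codes, "This trial is not blinded". The protocol describes no coding of arms for the analysis.

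On how the analysis file is made, Data Handling and Record Keeping says that questionnaires are double-entered and that "the laboratory data will be provided in electronic form and merged based on a common identifier". In the roles section, the CDC assists with "training, statistical analysis, and interpretation of results" and also supervises study procedures and data collection. Imperial College is listed only as assisting with statistical analysis.

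**The concern.** The reason and the conclusion do not match. Route of administration shows the arm to anyone who gives, receives or watches the vaccination. It shows nothing to a person whose only contact with the trial is a data file. The same paragraph makes the point itself: the laboratories are kept blind although the routes differ.

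The sentence states that blinding is impossible, so a statistical analysis plan that masked the analysts would contradict the protocol. That makes it a wrong statement rather than a detail left for later.

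At stake are decisions taken after the laboratory has reported. Blinded reading protects each assay result. It does not protect the choice of analysis set or the form of the endpoint if these are settled by someone who can see results by arm.

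**Working it through.** The protocol gives no figure on this point to reproduce, so the check is mainly a comparison of sections.

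**1. Does route unblind the analyst?** The analysis file comes from questionnaires and laboratory results joined on an identifier. Arm enters it as recorded data and can be replaced by a code. Route is therefore no obstacle.

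**2. Is anything left to choose?**

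- *Analysis set.* The section on missing data (see "All evaluable subjects will be included in the analysis") first defines evaluable children as those who complete everything and give enough serum. It then also admits those lacking a stool or gingival fluid sample. The withdrawal section agrees. The section on selection of subjects claims to restate the rule but limits the analysis to children who completed all requirements and visits, without that exception. Stool carries the primary endpoint, so the difference bears on the primary comparison.
- *Form of the primary endpoint.* The endpoint statement names days 3, 7 and 14 after the challenge. The Statistics section applies chi-square to types 1, 2 and 3 at each collection point, by arm and age group. Annex II, item 2, compares children who do or do not excrete after the challenge, by arm. The first two point to separate tests and the third reads as one overall outcome. No rule for combining the days is given.

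**3. What is already protected?** The laboratories are blind, and Annex II fixes a two-tailed chi-square with 95% confidence intervals. Blood collection and sufficiency are recorded facts on the case report form. Additional analyses need agreement among the participating institutions.

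**4. Would coding the arm column be enough?** No. The Day 0 form records vaccine type, lot and batch, injection site for IPV, and swelling and redness for IPV only. The adverse event form repeats vaccine type and lot. Some results may also hint at the arm. IPV is given as a three-part 40-8-32 formulation while bOPV contains types 1 and 3 only, and sera are tested for all three types, so day-28 type 2 titres could separate IPV from the other arms. Day-28 stool could contain vaccine virus from the day-0 bOPV dose.

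**5. How large could the effect be?** The documents do not say. As an illustration, suppose that two defensible definitions give standard normal test statistics z1 and z2 with correlation r under no effect, and that the better one is reported. The error rate is P(|z1| > 1.96 or |z2| > 1.96):

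| Assumed r | Error rate |
| --- | --- |
| 0.99 | 0.057 |
| 0.9 | 0.070 |
| 0.5 | 0.091 |

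The correlation is an assumption throughout. The calculation also supposes that the choice is made on the results, which nothing in the protocol says will happen.

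**The case against.** The case against is that this is one loose word in a trial openly declared unblinded, and that no stated analysis depends on it. Much of its support is sound:

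- The Statistics section covers every day and type, so on that reading nothing is selected. Any multiplicity that results is a separate matter which blinding would not cure.
- Evaluability rests largely on recorded facts, and the conflict between the two analysis-set sections needs reconciling whether or not the analyst is blind.
- Firm pre-specification would prevent selective choice without any masking.
- Coded-arm review and locking of programs are commonly placed in a statistical analysis plan, so their absence here is not a fault.
- Masking would be partial, above all for staff of the institution that also supervises data collection.

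These points limit the weight of the concern but do not remove it. The protocol does not merely omit analyst masking; it declares it impossible on a ground that does not apply. The two choices above are still open in the text. Partial masking still protects decisions made before anything is tabulated by arm, particularly for an analysis group with no listed field role.

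A reader might infer more: that the primary result is biased, that the error rate is 7%, or that recoding one column would cure the problem. The documents support none of these. Blinded laboratory reading and a fixed test argue against the first, 7% belongs to a single assumed correlation, and the forms carry several other fields that reveal the arm.

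**Conclusion.** The statement is wrong as far as statisticians are concerned and should be corrected. The residual risk is modest and confined to choices made after laboratory reading; measurement of the endpoint is not in question. Its size cannot be derived from the documents, and the error rates of roughly 6% to 9% are an illustration that should be shown as a range or left out. The conclusion assumes that the analysts can work from the merged file without attending vaccination visits. That fits a group listed only for statistical analysis better than one that also supervises the field work. The point is worth acting on because the safeguard is cheap, not because the trial's validity depends on it.

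**What to change.** Delete statisticians from the sentence in the section on measures to minimise bias. Add that, until the list of evaluable subjects, the endpoint derivation and the analysis programs are locked, the analysts receive a file in which:

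- the arm is coded;
- vaccine type, lot and batch, injection site, IPV-only local reactions, and the vaccine fields of the adverse event form are withheld;
- laboratory results that could reveal the arm, such as type 2 serology and day-28 stool, are held back where practical.

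Before the lock, reconcile the two analysis-set sections and state one form of the primary excretion endpoint.

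The cost is masking several fields and a short unblinding step before the final tables. Visits, samples, vaccines and sample size do not change. The protocol should acknowledge that masking will be incomplete, particularly for staff of the institution that also supervises data collection.

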## A description of trial treatment, dosage, dosage regimen of the investigational product, dosage form, packaging and labelling:

## A description of trial treatment, dosage, dosage regimen of the investigational product and dosage form is provided above.

## IPV (bulk source: NVI, Netherlands) and bOPV (bulk source: PT Biofarma) of Panacea Biotec Ltd. will be made available in the commercial packaging. IPV will be made available as single dose prefilled syringe and bOPV will be supplied as multidose vial for oral use. The batch numbers, expiration dates and physical description will be present on the label.

## Additional information will be added as given-

| FOR CLINICAL TRIAL PURPOSE ONLY |
| --- |
| Protocol Number: PBL/CR/2011/02/CT |
| Sponsor - Panacea Biotec Ltd. |

## The sponsor will supply the study vaccines. The investigator (or pharmacist) will make an inventory and acknowledge receipt of all shipments of study vaccines. All vaccines are to be stored in accordance with the instructions of the manufacturer.

The expected duration of subject participation, and a description of the sequence and duration of all trial periods, including follow-up:

The study participants will be enrolled for a total of ~60 days. No additional follow-up is planned.

## A description of "stopping rules" or "discontinuation criteria" for individual subjects, parts of the trial and the entire trial:

No stopping rules or discontinuation criteria appear necessary or are envisioned. The trial will be monitored by the Data and Safety Monitoring Board (DSMB), and serious adverse events will be reported according to GCP requirements to the sponsor within 24 hours, and to the respective regulatory agencies and ethical review committees within 15 days.

## Accountability procedures for the investigational product, including the comparator:

Comprehensive training of all study staff, and a detailed questionnaire will ensure and document that study protocol requirements are being followed. Vaccine will be stored according to cold chain requirements, and detailed inventory logs will be maintained.

## Maintenance of treatment randomization codes and procedures for breaking codes:

This trial is not blinded.

## The identification of any data to be recorded directly on the CRFs (i.e. no prior written or electronic record of data), and to be considered to be the source data:

A questionnaire (Annex IV) will serve as the primary data collection instrument, and will serve as the source data.

# Selection and Withdrawal of Subjects

All eligible children within the correct age group in the study area will be eligible to participate. Study participants may withdraw for any reason at any time. Withdrawal will not affect in any way the treatment of the child in the study institution.

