**Preamble**

With polio eradication making rapid progress, India is one of the four remaining polio-endemic countries and poses a unique challenge for global eradication due to extremely efficient poliovirus transmission . Until April 2005, the Polio Eradication Initiative in India, and globally, has relied exclusively on trivalent oral poliovirus vaccine (tOPV). In 2005, first monovalent type one oral poliovirus vaccine (mOPV1) and then mOPV3 were used for the first time in large-scale campaigns in India to boost humoral & intestinal immunity. In 2009, a new bivalent (type 1+3) OPV (bOPV) was licensed in India, and will be used extensively in the country in 2010, following the recommendations of the Advisory Committee on Polio Eradication (ACPE) [1].

A trial conducted during May 2009 in Moradabad district, Uttar Pradesh, India, showed that > 99% of children 6-9 months of age had detectable antibodies against poliovirus type 1. These results suggest that the strategy of providing mOPV1 through monthly immunization rounds with high coverage is successfully achieving high population immunity. However, these results raise the question of why this high level of population immunity did not interrupt the remaining chains of poliovirus transmission, and children still get infected with wild poliovirus in Uttar Pradesh. Is it possible that insufficient or waning mucosal immunity allows transmission of poliovirus among children who are otherwise protected against paralysis? And, can we boost mucosal immunity in these children to decrease the circulation of virus?

The proposed trial will evaluate mucosal immunity before and after receipt of two different poliovirus vaccine types, in children living in areas at high risk for poliovirus infection. This trial will be conducted after approval from the Indian Regulatory Authorities, Drugs Controller General of India [DCG(I)], and the relevant ethical review committees.

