# Trial Design

Local community mobilization coordinators (CMCs) working with the Global Polio Eradication Initiative (GPEI) will identify families with children in the target age-group (i.e. 6-11 months, 5-6-years, and 10-11-years). Surveillance Medical Officers (SMOs) will visit households of potential candidate families, explain the study to the parents or guardians, and facilitate transportation to one of the study sites for those interested to participate. Approximately 10 study sites will be chosen in areas identified as high-risk for poliovirus transmission.

At the study site, a physician will conduct a short interview and physical examination. After obtaining informed consent from the parents (and assent from children of age 10-11 years), the study participant will be assigned a study number and allocated to a study arm. For this, the parent or child will select a closed envelope that includes the study arm from a basket. Then a baseline blood sample collected by venipuncture, oral (crevicular) fluid, and stool samples will be collected before vaccine administration.

Note: crevicular fluid will not be collected in the 6-11 month age group because of the absence of teeth.

In a subset of children 10-11 years of age (~175-200 children) a second blood sample will be collected at 7 days by venipuncture for the ELISPOT test.

In all children, at 28 days, another blood sample by venipuncture, another oral (crevicular) fluid sample and a stool sample will be collected before the subjects receives the challenge vaccine (bOPV). Thereafter, at days 3, 7 and 14 stool samples will be collected. And finally, at day 56, another serum sample and oral fluid sample will be collected. At this time, having fulfilled the study requirements, the children will exit the study.

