## The level of significance to be used:

We are seeking to show (a) a reduction in number of subjects excreting vaccine poliovirus following a challenge vaccine dose (bOPV) among those vaccinated with bOPV or IPV compared to the control group; (b) an increase in secretory IgA following vaccination with bOPV or IPV compared to a control group; and (c) an increase in seroprevalence or antibody titers following vaccination with bOPV or IPV compared to a control group.

We use a level of significance of 0.05 (two-tailed test) and a power of 90% to detect the │20%│difference in proportion of subjects shedding vaccine poliovirus after the challenge dose of bOPV(see annex I).

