# ANNEX I

Sample size calculations

1. We are seeking to demonstrate that excretion of poliovirus following a challenge with bOPV is significantly lower in the bOPV or IPV vaccinated groups compared with the control group.

2. Definitions: (a) Significantly decreased defined as a decrease of ׀20%׀ in the proportion of study subjects vaccinated with IPV or bOPV who excrete virus following a challenge dose of bOPV compared with the proportion of control subjects who excrete virus after the challenge.

3. Applying a power of 0.90 (beta) and an alpha of 0.05, the following samples sizes would be required based upon assumed excretion of control and treatment (IPV or bOPV) groups:

| Control group excretion | bOPV or IPV excretion after challenge dose | | |
| --- | --- | --- | --- |
| 0.10 | 0.20 | 0.30 |
| 0.30 | 89 |  |  |
| 0.40 |  | 119 |  |
| 0.50 |  |  | 134 |

5. Using the most likely approach of low excretion in control and treatment groups due to previous exposure to OPV in all subject), we would require a sample of 89 for each study group, for a total of 801 subjects for the 3 study arms and 3 age groups per study arm.

6. With a sample size of at least 89 per study group, we should have a probability of 0.89 or more of estimating any of the differences in excretion of vaccine virus after the challenge dose within a ׀absolute value 20%׀

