# DOB: ____ \ _____ \ _____ Age: ______ years ______ months Sex: F / M

Religion: H / M / O Father’s occupation:

Father’s education (encircle): Illiterate / Primary / Middle / Tenth / Twelfth / Graduate

Number of people in household (parents & siblings only): ­­

Number of children <5 years in household (study subject):

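### Nothing stops siblings from joining in different arms, so a control or IPV child can pick up vaccine virus at home around its challenge; the likely loss is small and a one-child-per-household rule avoids it.

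*Protocol*

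**What the plan says.** **Recruitment and eligibility.** Under Trial Design, community mobilisers look for families with children aged 6-11 months, 5-6 years or 10-11 years, and field officers visit the households. Selection and Withdrawal of Subjects adds: "All eligible children within the correct age group in the study area will be eligible to participate".

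**Allocation.** Under Trial Design, "the parent or child will select a closed envelope that includes the study arm from a basket". The unit is the child.

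**Household rules.** The inclusion criteria, the exclusion criteria and the eligibility list on the enrolment questionnaire (Annex V) contain none. Their only family-level items are planned absence or travel and immunodeficiency in a family member.

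**Household data.** The Day 0 form records the number of people in the household and "Number of children <5 years in household (study subject"). It does not ask whether another household member is enrolled, or in which arm.

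**Exposure.** Arm A receives live bOPV on day 0, and every child receives bOPV on day 28 as the challenge. The primary endpoint is excretion at days 3, 7 and 14 after the challenge. The Preamble says that India "poses a unique challenge for global eradication due to extremely efficient poliovirus transmission", and the design justification treats mucosal immunity as a barrier to excretion and community spread.

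**Sample size.** The significance section reads "We use a level of significance of 0.05 (two-tailed test) and a power of 90"%. Annex I takes 0.30 excretion in controls against 0.10 in a vaccinated arm, 89 per arm and age group, with a stated probability of 0.89 or more at that size.

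**The concern.** The comparator is meant to be unvaccinated until its challenge, and the IPV arm is meant to have had IPV only. Live virus given on day 0 to a sibling in the bOPV arm can reach such a child during days 0 to 28. A participant from the same home who enrolled earlier and has already been challenged is a second source, and that virus can arrive before day 28 or during the day 31-42 stools.

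Uptake before the challenge can immunise a control child and lower its excretion, which shrinks bOPV versus control. It also touches the day-28 sIgA and serology endpoints. Virus acquired after the challenge can be counted as failure to resist the child's own dose; stool typing identifies the Sabin type, but no rule assigns an isolate to the child's own dose or to a contact.

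The planned chi-square tests also treat children as independent, which siblings are not. Each age band is about one year wide, so siblings will mostly sit in different bands. The dependence therefore matters mainly where ages are pooled or compared.

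Eligibility and the unit of allocation are fixed in the protocol. No later analysis can restore a control arm that has been exposed.

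**Working it through.** **1. The plan's own figure.** Inputs from Annex I: "Applying a power of 0.90 (beta) and an alpha of 0.05", control p1 = 0.30, vaccinated p2 = 0.10, n = 89 per group.

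- Unpooled variance, no correction: (1.960 + 1.282)² × (0.21 + 0.09) / 0.20² = 78.8.
- With continuity correction: (78.8/4) × [1 + √(1 + 4/(78.8 × 0.20))]² = 88.5, rounded up to 89. This reproduces the stated size.
- Power at 89, pooled variance under the null and continuity-corrected: Φ{[(p1 − p2) − 1/n − 1.960 × s0] / s1}, where s0 = √(2 × 0.20 × 0.80 / 89) = 0.0600 and s1 = √((0.21 + 0.09)/89) = 0.0581. This gives Φ{(0.200 − 0.0112 − 0.1175)/0.0581} = Φ(1.227) = 0.890, which matches the stated 0.89. Without correction it is 0.92.

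**2. Chance of a bOPV sibling.** With independent draws in the ratio 1:1:1, two enrolled siblings land in different arms with probability 2/3. A control or IPV child with one enrolled sibling has a 1/3 chance that this sibling is in arm A.

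**3. Share of controls immunised, f.** The documents give neither the share of children with an enrolled sibling (h) nor a household spread rate. Assume that the 0.30 excretion which Annex I expects in previously OPV-exposed controls also applies to arm A after its day-0 dose, and that every shedder immunises its contact. Then f = h × 1/3 × 0.30 = 0.10h.

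- h = 20%: f = 2%
- h = 50%: f = 5%
- h = 100%: f = 10%
- Two enrolled siblings for every control: f = 1 − (1 − 0.10)² = 19%

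These are upper values for each h, because not every shedder transmits and the contacts have had OPV themselves. They cover the day-0 route only; the route through an earlier-challenged participant is not quantified.

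**4. Effect on bOPV versus control.** If an immunised control excretes at 0.10, the control rate becomes 0.30 − 0.20f. Power at n = 89 per group:

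| f | control rate | difference | power, corrected | power, uncorrected |
|---|---|---|---|---|
| 0 | 0.300 | 0.200 | 0.89 | 0.92 |
| 2% | 0.296 | 0.196 | 0.88 | 0.91 |
| 5% | 0.290 | 0.190 | 0.86 | 0.90 |
| 10% | 0.280 | 0.180 | 0.83 | 0.87 |
| 19% | 0.262 | 0.162 | 0.75 | 0.81 |

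**5. IPV versus control.** Both arms can be exposed, so both rates may move. The calculation changes the control rate only and gives neither size nor direction for this contrast.

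**The case against.** **It rests on silence.** The protocol nowhere says that siblings will be enrolled, and the openness sentence is generic. This stands: the plan permits co-enrolment but does not announce it.

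**A large loss is tempting but not supported.** A reader might infer that 20-30% of controls could be immunised, with uncorrected power of 0.80 to 0.70 (0.74 to 0.63 corrected). With a 1/3 chance of an arm A sibling, f = 30% needs about 90% of controls to have one enrolled sibling and every such sibling to immunise its contact. Under Annex I's own 30% excretion, one enrolled sibling per control cannot give more than about 10%. Higher shedding in infants, or two enrolled siblings, would raise this, but the large values are not credible central cases.

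**The contamination is partly visible.** Stools and sera are taken on day 0 and on day 28 before the challenge, in controls too. Father's name, address and village on the enrolment form would allow siblings to be linked later. This stands in part: no rule uses these data, and a single day-28 stool misses shedding that has already ended.

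**Other exposure is larger.** Campaign doses and neighbours expose all arms, and a household rule leaves that untouched. This stands, but co-enrolment is the part that the sponsor controls.

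**The bias is mainly conservative, and pooling ages leaves power to spare.** The first part holds for bOPV versus control before the challenge. Siblings enrolled together are also all challenged on the same day, so later spread between them is largely non-differential. With ages pooled (3 × 89 = 267 per arm), power stays near 0.99 even at f = 30%. But Annex I sizes each arm within each age group, and there the reserve is thin: with 20% drop-out, 110 × 0.80 = 88 remain.

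**Conclusion.** The gap is real: followed as written, the protocol can place siblings in different arms of a trial of a live, shed vaccine virus, and its forms do not flag it. The effect is a modest bias toward no difference for bOPV versus control, an uncertain one for IPV versus control, and some loss of independence between children.

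The probable cost is a few percent of controls and about one to three points of power in an age-group comparison (0.89 to 0.88 at 2%, 0.86 at 5%), with 0.83 as the limit for one enrolled sibling. This rests on assumed co-enrolment and on reading Annex I's 30% as shedding after the day-0 dose.

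The documents do not support saying that contamination will occur on a large scale, that it necessarily shrinks the IPV effect, or that the trial is invalid. The change is worth making because it is cheap and cannot be made after enrolment.

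**What to change.** Add to the inclusion or exclusion criteria, and as an item on the enrolment eligibility form, that only one child per household is enrolled and that no child living with a current participant is enrolled. State what counts as a household, for example a shared kitchen.

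The cost is one eligibility line and one form item in an amendment, slightly slower recruitment, and some families told that only one child can join. The total of 990 and the planned tests stay as they are, and the independence assumption is better protected.

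Allocating whole households by a single envelope is not a good substitute. It creates clusters, and the protocol states neither a design effect nor a clustered analysis for them. Exposure from neighbours and campaigns remains under either approach and should be acknowledged when the results are interpreted.
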